### Study Setting

The study will be undertaken in collaboration with four community child and family health organizations (study sites) in two Australian cities located in separate states/territories. There are two study sites in each city. Three of these organizations have an explicit focus on perinatal mood problems, all offer COS-P in their suite of services for families with young children (aged 0-5) and all expressed an interest in participating in a collaborative evaluation study. See Table 1 for site details. All study sites routinely deliver COS-P groups, generally four times per year during school terms. All sites offer COS-P to current clients, and two also make the program available to parents from the community. One site delivers COS-P to clients only toward the end of other treatment, whereas the other three do not specify timing for the intervention. In all cases, group facilitators use their clinical judgement to assess suitability for the group, based on prior casework and/or a pre-group interview (face-to-face or by phone).

**Table 1 T1:** Overview of study sites.

	**Site 1 Tresillian Family Care Centres**	**Site 2 Raphael Services NSW St John of God Healthcare Social Outreach**	**Site 3 ACT Health Perinatal and Infant Mental Health Consultation Service**	**Site 4 Marymead Centre for Early Life Matters**
Type of service	Early parenting support	Perinatal and infant mental health	Perinatal mental health	Early parenting support
Referral pathway/s	•Health professionals •Self-referral for groups	•General practitioners and medical specialists	•Health professionals	•Health professionals •Education professionals •Self-referral
Accessed by parents with…	Parenting challenges, often around feeding, sleeping, settling, adjustment & associated perinatal mental health issues	Mental illness in the perinatal period (pre-conception to index child age 4)	Perinatal mood disorders (pregnancy to 12 months post-partum)	Concerns about parenting, adjustment, mental health, or child relationship, emotional, or behavioral issues
Child age range	0–5 years	Pre-conception to 4 years old	0–5 years	0–8 years
Professional staff	•Nurses •Social Workers •Psychologists •Psychiatrists/Registrars •Pediatricians •GPs	•Psychiatrists/registrars •Clinical Psychologists •Social Worker •Mental Health Nurses	•Medical Officer •Psychiatrists/Registrars •Psychologists •Social Workers •Occupational Therapists •Nurses	•Psychologists •Social Workers •Counselors
Where does COS-P fit into treatment?	•Referral pathways from residential & day stay services •Stand-alone parenting program	•Offered toward end of treatment	•During and toward end of treatment	•Stand-alone parenting program
Who delivers COS-P?	•Allied Health staff •Nurses •Psychiatry Registrars (rarely)	•Psychiatrist/registrar •Social workers •Mental health nurses	•Allied Health staff •Mental health nurses	•Psychologists •Social workers •Counselors
Who can access COS-P?	•Clients •Parents in the community	Clients only	Current and recent clients only	•Clients •Parents in the community
Cost of COS-P	AUD88 (waived in cases of financial hardship)	No cost	No cost	No cost

Following development of a research proposal, meetings were held with management (and lead clinical staff, in some cases) at each organization, to discuss the study and its feasibility in each setting. The study design, procedures, and measures were finalized in collaboration with representatives of each of the study sites.

### Participants

Eligible participants will be primary caregivers and/or their partners, with a child aged 0–60 months (at study entry), who are registered to attend a COS-P group at one of the study sites during the 18–24 month study period. Study exclusion criteria (an acute disorder or one likely to limit participation; insufficient English proficiency to complete study measures) are, in fact, also site exclusion criteria for referral to COS-P groups. They are routinely assessed at the time of engagement with the organization and also during routine pre-group-enrolment screening. Any participant whose assessment indicates risk to parent or infant will be triaged into other appropriate treatments. Thus, the single study-specific exclusion criterion is having attended COS-P sessions prior to study enrolment. Participants will receive no reimbursement for study participation.

### Procedure

All eligible clients will be offered the opportunity to participate in the study as soon as is practical after their registration for COS-P. In most cases, administrative or clinical staff will explain the study and invite participation during their routine pre-group contact with clients. In both cities, a locally-based member of the research team will provide study oversight and research support, including assistance with participant recruitment and administration of study measures, as required by study sites.

Study measures will be administered by site clinicians and members of the research team, all of whom will receive related training and written instructions. Personnel administering measures in each case will depend on site capacity. Two study questionnaires will be administered to all study participants; interviews and observational procedures will be administered only to the subsample of participants who consent to and can complete these additional measures within the required timeframe. Treatment group participants will complete study measures a maximum of 2 weeks before the first session (Time 1) and a maximum of 2 weeks after the final session (Time 2) of their COS-P group. Those completing only study questionnaires will complete them at the relevant COS-P session (i.e., Time 1 at the start of session 1 and Time 2 at the end of session 8). Waitlist control group participants will complete both Time 1 and Time 2 study measures within the same 7 to 11-week timeframe, before they commence COS-P. Waitlist-control group participants completing only questionnaires will complete them onsite, if possible, otherwise they will be mailed hard copies or emailed individualized links to online versions of the Time 1 and Time 2 questionnaires. The latter process will be managed by the first author, using the university's password-protected Qualtrics platform. A separate record of individualized links by Client ID will enable matching of Time 1 and Time 2 data, and linking with clinical file data. De-identified questionnaire data for these participants will be stored securely in Qualtrics. All participants completing additional interview and/or observational procedures will complete these assessments at their study site or in their home, depending on site capacity, and participant convenience. For participants completing the observational assessment, time of day will be kept consistent between Time 1 and Time 2 assessments, to the extent possible considering parents' availability constraints and the unpredictability of infant/child sleep-wake cycles. See Figure 2 for study flow.

**Figure 2 F2:**
[figure not shown]
Flowchart detailing participant flow through study, including timing of measures and intervention.

The study interview will be audio recorded and will take approximately 1 h to complete. Time 1 and Time 2 interviews for each participant will be administered by two different members of the research team, as required by the nature of the interview and associated coding system. Since the time between interviews is relatively short, and participant elaboration vs. more truncated responses can be meaningful in coding, it is important that participants do not reduce the detail in their Time 2 answers due to a perception of interviewer familiarity from Time 1. While we acknowledge the potential for interviewer-related bias with this approach, evaluation of test-retest reliability of a similar narrative interview with different interviewers at each time point found no interviewer effects (47, 48). To maximize consistency of administration, and thus minimize the risk of systematic bias in the current study, interviewers will undergo training and receive regular research support (see below), will use a standardized interview template and written protocol, and will undertake a mix of Time 1 and Time 2 interviews for both treatment and control group participants. For treatment group participants, where possible, the site clinician scheduled to facilitate their COS-P group will administer Time 1 (pre-group) interviews and video assessments, and a member of the research team will administer Time 2 (post-group) interviews and video assessments. For control group participants, administration personnel will be reversed. A participant's COS-P group facilitator will never administer their post-group study interview, to reduce risk of associated response bias.

The observational procedure is a 5-min caregiver-child free play interaction (video recorded), detailed in a written protocol with illustrations. Caregivers will be given the instruction, *play with your child as you would if you had a spare 5- minutes at home*. Two consistent toys will be provided—a baby doll with clothes, and a train with detachable carriages—and caregivers will be told they may use these toys if they wish. For children up the age of 12 months, caregivers will be requested to place the child in a fixed seat (e.g., car chair or high-chair) and to sit opposite the child with their face at the child's face level. For children aged 13 months and up, caregivers will be requested to sit opposite their child on the floor.

Pre-specified additional participant data will be retrieved from clinical files at each site by senior clinicians/managers and sent to the research team using client study ID only (permission granted as part of study consent process). These data comprise country of birth, living situation (single, cohabiting), number of children, history of mental health problems (if disclosed), current medication for mental health disorder, and (via chart audit) additional treatment/service received during study participation, including non-group COS-P content. Study processes will be documented to enable a *post-hoc* process evaluation (37).

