### The Current Study

The primary aim of the current study is to examine the effectiveness of COS-P for caregivers who present to early parenting support services with parenting concerns, often in the context of PND. Study outcomes have been selected with reference to a recently developed theory of change for COS-P (46), which proposes that COS-P works to improve aspects of caregiving that may be necessary prerequisites for secure attachment, including caregiving representations (i.e., how the caregiver thinks and feels about the child, themselves as a caregiver, and their relationship with the child) and child-focused mentalization (the ability to be aware of and make inferences about mental states of self and child, and their impact on behavior). These components of relational caregiving capacity are theorized primary outcomes of COS-P. Changes in parent behavior, and in child attachment and/or behavior are not directly targeted by the intervention, but may be longer-term outcomes of targeted improvements in caregiving, and thus are considered secondary outcomes (46).

We aim to establish if COS-P is effective in building caregiving capacity through an increase in (a) positive representations of the child and self as caregiver, (b) more accurate caregiver mentalization, (c) more responsive caregiving behavior, and (d) reduction of caregiver depression symptoms. We hypothesize that caregivers receiving COS-P will show greater improvements in these areas than caregivers in a waitlist condition.

Given that COS-P research to date includes disparate (and often small) samples with a range of risk factors, we also intend to examine whether socio-demographic (e.g., caregiver language background, gender, education level, child age) and psychosocial (e.g., severity of depression symptoms) risk factors moderate response to the intervention, to extend knowledge of what works for whom. Due to limited empirical data available on COS-P outcomes, we do not posit directional hypotheses regarding the moderating effects of examined demographic and psychosocial risk factors.

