### Data Analysis

Given that this is not a randomized trial, an intention to treat analysis is not essential. To maximize understanding of what works for whom, we seek to measure the intervention effect on those participants who actually receive the intervention—and we also seek to understand the factors that influence completion and non-completion of COS-P, as well as variations in response (71). Thus, data in this study will primarily be analyzed to measure the treatment effect on participants who received COS-P as intended. Complete Time 1 and Time 2 data for study participants who attend at least six of the eight COS-P sessions will be included in these analyses, together with data from clinical files and information collected during facilitator fidelity interviews, if appropriate. For participants who (a) attend 5 or fewer COS-P sessions and/or (b) do not complete Time 2 measures, treatment effect will not be measured; only Time 1 data, clinical file data and information collected during facilitator fidelity interviews will be analyzed, to explore whether characteristics of these caregivers distinguish them from completers and/or influence failure to complete the intervention.

Analyses will be conducted using SPSS Version 26 (72). Descriptive analyses will be used to profile and compare the characteristics of the treatment and waitlist control groups in the four participating sites. Bivariate correlations and independent samples *t-*tests will be used to explore relationships among the outcome variables and any potential covariates. As group allocation is not randomized, and recruitment is undertaken across four sites with different characteristics, the two groups may differ on distribution of demographic and risk factors which may impact on intervention effects. Baseline comparability will be assessed using independent samples *t*-tests (for continuous variables) and chi-square tests of independence (for categorical variables). Mixed design ANOVA will be used to control for any observed differences in baseline characteristics. Due to anticipated differences among participant cohorts from the four different sites, child age and depression symptoms (EPDS score at Time 1) will be included as *a priori* covariates. If sample size and composition allow, results will be stratified by site.

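### Clinician and researcher interviewers are used in opposite order in the two arms, so any interviewer-type effect is confounded with the group-by-time effect and enters it twice

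*Protocol article*

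**What the plan says.** The rule is in the Procedure section of the protocol article, in the paragraph on the study interview that follows Figure 2.

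- Treatment arm, Time 1: "For treatment group participants, where possible, the site clinician scheduled to facilitate their COS-P group will administer Time 1 (pre-group) interviews and video assessments".
- Treatment arm, Time 2: "a member of the research team will administer Time 2 (post-group) interviews and video assessments".
- Control arm: "For control group participants, administration personnel will be reversed". Controls therefore see a researcher at Time 1 and a clinician at Time 2.

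The same paragraph acknowledges that interviewers may introduce bias. It relies on training, a standard template, a written protocol and the provision that interviewers "will undertake a mix of Time 1 and Time 2 interviews for both treatment and control group participants". It also cites outside evidence: "evaluation of test-retest reliability of a similar narrative interview with different interviewers at each time point found no interviewer effects". It bars a participant's own group facilitator from the post-group interview.

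The hypothesis, in The Current Study, is that "caregivers receiving COS-P will show greater improvements in these areas than caregivers in a waitlist condition". The Data Analysis section plans a mixed design ANOVA with child age and Time 1 EPDS as a priori covariates, and names no interviewer term.

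**The concern.** The reversal looks like counterbalancing, and for the main effects it is: clinicians and researchers are spread evenly over arms and over time points. But the hypothesis concerns the difference between arms in change over time, and on that contrast the reversal has the opposite of its intended effect. All treatment-arm changes run from clinician to researcher and all control-arm changes from researcher to clinician. Any tendency of caregivers to speak or behave differently with a clinician than with a researcher therefore appears as a treatment effect, or cancels one.

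The protocol itself regards such an effect as plausible. It says that "participant elaboration vs. more truncated responses can be meaningful in coding", and it keeps the facilitator away from the post-group interview because of response bias. Yet the Time 1 score, which the facilitator collects in the treatment arm, enters the change score with the same weight as Time 2.

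The outcomes exposed are the COSI caregiving representations and both mind-mindedness measures (primary) and observed interaction quality (secondary). These are the measures that do not depend on self-report questionnaires.

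**Working it through.** The protocol gives no figure for this point, so there is none to reproduce. The check is structural, followed by an illustration of size.

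**Step 1: cell means.** Let τ be the true effect, δ the change over time common to both arms, and R and C the mean shifts in score with a researcher and with a clinician.

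| Arm | Time 1 | Time 2 | Expected change |
|---|---|---|---|
| Treatment | clinician | researcher | τ + δ + (R − C) |
| Control | researcher | clinician | δ + (C − R) |

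Difference in change = τ + (R − C) − (C − R) = **τ + 2(R − C)**.

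**Step 2: can a model separate them?** Code group (1 = treatment), time (1 = Time 2) and clinician (1 = yes). Over the four cells, clinician = group + time − 2 × (group × time). Check:

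- treatment, Time 1: 1 + 0 − 0 = 1
- treatment, Time 2: 1 + 1 − 2 = 0
- control, Time 1: 0 + 0 − 0 = 0
- control, Time 2: 0 + 1 − 0 = 1

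The matrix with columns intercept, group, time, group × time and clinician has rank 4 with 5 columns. An interviewer term cannot be estimated alongside the interaction.

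**Step 3: size, under assumed values of R − C.** The Sample Size Calculation section gives 40 analysed and a Time 1–Time 2 correlation of 0.5. I assume 20 per arm. The SD of change is √(2(1 − 0.5)) = 1 SD. For a two-sided 5% t test on change scores (38 degrees of freedom) with no true effect, the noncentrality is bias × √(20/2).

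| Assumed R − C (SD) | Bias = 2(R − C) | Noncentrality | False-positive rate |
|---|---|---|---|
| 0 | 0 | 0 | 5% |
| 0.10 | 0.20 | 0.63 | 9.5% |
| 0.20 | 0.40 | 1.26 | 23.4% |
| 0.25 | 0.50 | 1.58 | 33.8% |
| 0.30 | 0.60 | 1.90 | 45.6% |

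A simulation of 5,000 trials gave 10.0% and 24.5% for 0.1 and 0.2 SD, in reasonable agreement. With the opposite sign the bias hides benefit: a true 0.5 SD (the usual reading of a medium effect) with R − C = −0.2 would be estimated as 0.5 − 0.4 = 0.1 SD.

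**Step 4: partial adherence.** Suppose the rule is followed for fractions p_t and p_c of the two arms, with researchers at both times otherwise. The bias is then (p_t + p_c)(R − C): 2 times at full adherence, 1.5 times at 75% in each arm, 1.0 times at 50% in each arm.

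**Step 5: same order in both arms.** With clinician at Time 1 and researcher at Time 2 throughout, the difference in change is τ + (R − C) − (R − C) = τ. In the simulation the rejection rate under this order was 4.5%.

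**The case against.** **The rule is not absolute.** It applies where possible, and the Procedure section lets personnel depend on site capacity. This stands: exact confounding holds only where the rule is followed. Departures shrink the bias in proportion, as step 4 shows, but do not remove it. If site capacity drives them, they also tie interviewer type to site.

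**Safeguards are stated.**
- The mix of interviews does not break the alias. Under the reversal, clinicians fill treatment Time 1 and control Time 2, and researchers fill the other two cells. If the mix was meant to cover all four cells, it contradicts the reversal.
- The cited evidence bears on how large R − C may be. As described, it concerns different interviewers at each time point, not a treating clinician against a researcher.
- Coding from de-identified transcripts may protect the coders, but not what the caregiver said.

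**The size is assumed, and so is its sign.** This stands. The false-positive figures are illustrations, and the bias could equally run against the intervention.

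**The scope is limited.** This also stands. The CCQ and EPDS are untouched, and the subsample target is 48 of 154. An administrator effect is less plausible in a five-minute play session with fixed toys and a fixed instruction than in a one-hour interview.

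**The remedy is not perfect.** Same order removes the bias only if R − C is equal in both arms. A clinician about to lead a caregiver's group may affect answers differently from one seen by a caregiver still weeks from starting. If so, the bias is the difference between the two arms' role effects, whereas under the reversal it is their sum.

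**Conclusion.** The concern holds and should be put right before further interviews are done. As written, the rule makes interviewer type inseparable from the group-by-time contrast, with a bias of 2(R − C). That result is algebraic and assumes only that interviewer type has an additive effect. How much it matters depends on R − C, which the protocol does not give; at an assumed 0.1 to 0.2 SD the bias is 0.2 to 0.4 SD. The analysis cannot repair this afterwards where the rule was followed. The bar on facilitators at the post-group interview is sound, but it does not require reversing the order for controls.

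The paragraph also needs reconciling with itself. It says elsewhere that the two interviews are given by two different members of the research team, which sits awkwardly with the site-clinician rule.

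**What to change.** 1. Replace the reversal with one order for both arms: where possible, a site clinician at Time 1 and a research team member at Time 2, for interviews and videos. Each participant still has two different interviewers, and the facilitator still never does the post-group interview.
2. Reword the sentences on mixed interviews and on two research team members so that they agree with this rule.
3. Record interviewer type (own facilitator, other clinician, researcher) at every assessment.
4. For assessments already done under the reversal, state the confounding openly. Report a sensitivity analysis with an interviewer-type term where departures from the rule make it estimable, allowing for site. Some may already exist, since the Sample Size Calculation section refers to questionnaire data from the first 67 intervention participants.
5. Draw conclusions from the between-arm comparison only. Under a common order, within-arm change contains the interviewer-type effect.

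The cost is mainly a change of rota. Under either scheme each participant has one clinician and one researcher assessment, so apart from drop-out before Time 2 the workload of each role is the same. Scheduling is slightly less flexible, because researchers do all Time 2 visits. Balancing both orders within each arm in equal proportions would also work, but in the treatment arm it needs a clinician other than the facilitator at Time 2.
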